### Participant Timeline

The participants will be reviewed monthly until the 32-week gestation period and then fortnightly until delivery, coinciding with scheduled antenatal visits where possible. The trial flow chart is depicted in Multimedia Appendix 4. The flowchart describes the participant's progression through the trial protocol and depicts the timing of the interventions.

### Sample Size

There are limited data on this topic, particularly on the estimated risk reduction in event rates. We intend to pilot the RCT with an initial 48 patients. This data will be used to refine the protocol and optimize logistics and will be used to inform a larger RCT.

### Randomization, Allocation, Concealment, and Blinding

The participants will be individually randomized via a telephone call to the National Health and Medical Research Council’s Clinical Trials Centre at Sydney University, who are independent of the trial, by the study coordinator. Randomization will be based on a minimization method with stratification for previous preeclampsia, personal history of gestational diabetes, and BMI≥35, to either CPAP, PT, or control groups. A maximum imbalance value of 1 between any of the 3 arms will be used in determining whether a forced allocation (ie, to achieve minimization of difference of stratification factor totals) or random allocation is used in a specific subject randomization. Treatment allocation will be unblinded for both study staff and participants.

### Data Collection, Management, and Analysis

The complete schedule of study visits, procedures and data collection points is presented in Multimedia Appendix 5, which depicts the trial participant study visits and intervention schedule.

### Data Management

Data from Apnealink screening tests, CPAP, and PT will be stored in a deidentified format. Polysomnography data will be stored on the secure hospital network. The system is secured via the Information Management and Technology Division’s corporate backup software. Research Electronic Data Capture (REDCap; Vanderbilt University) database [32] will be used for data collection and management. Questionnaires will be completed electronically by participants via an email link where possible or by paper questionnaire where needed. In the event of participant discontinuation from the RCT, long-term fetomaternal outcomes of interest will be collected, where agreed to by participants during consent, in writing.

### Data Collection Methods

#### Blood and Urine Collection

With consent, blood will be collected at 12-16, 16-20, 28 gestation weeks, and 6-12 months post partum by study staff or using hospital pathology collection services in EDTA tubes. The blood will be centrifuged (3000 rpm, 10 min), and plasma will be aliquoted (250 µL). The buffy coat will be collected and stored in approximately 250 µL RNA. Later, all specimens will be snap frozen in liquid nitrogen and stored at –80C at the Ingham Institute of Medical Research (Liverpool, New South Wales, Australia). Biomarkers (sFlt-1 [soluble fms-like tyrosine kinase 1], PlGF [placental growth factor], IL-6 [interleukin-6], TNFα [tumor necrosis factor alpha], and HIF1α [hypoxia-inducible factor 1-alpha]) will be assayed at the conclusion of the study blinded to outcomes.

Urinalysis will be conducted at each study visit using SIEMENS Multistix 10SG Test strips. A score of negative, trace, 30 mg/dL (++), 100 mg/dL (++), 300 mg/dL (++), or >2000 mg/dL (+++) will be recorded. If greater than 1+ protein is detected, a random spot urine sample will be sent to hospital pathology services for measurement of urinary protein adjusted for creatinine excretion.

#### Fetal Monitoring

Fetal ultrasound will be undertaken at the study site fetomaternal units (FMUs). Uterine artery blood flow (pulsatility index measurements) will be recorded at the randomization visit (12-16-week gestation period), 2-6 weeks later (average 4 weeks to 16-20-week gestation period), and at 36-week gestation period. Morphology scan (16 weeks) (may be combined with uterine artery blood flow) and growth scan (36 weeks) will be performed. Fetomaternal scans performed at study sites will be performed using ViewPoint 6 (General Electric Healthcare) by experienced sonographers supervised by physician consultants within the FMU.

#### Questionnaires

ESS [33] and STOP-BANG (snoring, tiredness, observed apnea, high BP [STOP] and snoring, tiredness, observed apnea, high BP-BMI, age, neck circumference, and gender) [34] questionnaires will be used in baseline screening and scored according to standing scoring recommendations (sum of 8 item-scores [ESS] and score 0-8 [STOP BANG]). Functional outcomes of sleep will be assessed using the Functional Outcomes of Sleep Questionnaire (FOSQ-10) [35], which has been validated in pregnancy and scored according to FOSQ-10 marking guidelines [36]. Questionnaires assessing sleep study acceptability, sleep study preference, and therapy acceptability will be undertaken and are presented in Multimedia Appendices 6-13. Questionnaires will be emailed to participants using REDCap or completed in paper hardcopy where the patient is unable to complete electronically. The acceptability questionnaires used in this trial were evaluated on hospital staff unaffiliated with the trial. Feedback was implemented, and questionnaires were redesigned before SWSLHD HREC approval and implementation.

#### Sleep Study Data Collection

The participants will undergo attended polysomnography (with therapy device in situ for CPAP and PT arms) using Grael v2 (Acquisition System, Compumedics), unattended polysomnography using SOMTE v2 (Acquisition system, Compumedics) and Apnealink Air (Resmed) at 28- to 32-week gestation period at LPH. Laboratory-based polysomnography will be repeated 6-12 months post partum.

Attended and unattended polysomnography will be scored using Profusion PSG 4 auto analysis software (Compumedics) by a single experienced sleep scientist using the 2020 AASM Manual for the scoring of sleep and associated events (Version 2.6 guidelines). Apnealink Air will be automatically scored using Airview (Resmed; AASM 2012, Automatic Scoring) and manually scored by a single experienced sleep scientist using 2020 AASM guidelines (events Version 2.6). All sleep study sets will be reported by the same sleep physician for consistency. Unattended polysomnography and Apnealink Air studies will be scored and reported blindly by sleep scientists and reporting sleep physicians.

Apnealink Air data collection includes airflow (pressure transducer), respiratory effort (abdomen) and oximetry (SpO_2_), snoring, and pulse. The participants will complete a self-setup in the home, will be provided with an instruction sheet, and will also manually start study recording as close to anticipated sleep onset as possible and manually stop recording at sleep offset.

Unattended polysomnography data collection included electroencephalography (F3 and F4, M1 and M2), electrooculography (E1 and E2), electromyography (EMG chin [submentalis]), electrocardiogram (modified lead II), airflow (pressure transducer), snoring, airflow (thermistor), respiratory effort (abdomen and thoracic), anterior tibialis EMG (left and right leg), oximeter (SpO_2_), and position sensor. The participants will complete a self-setup at home. A comprehensive instruction booklet will be provided, and the participant will be encouraged to watch an instructional video [37]. The participants will have access to phone or video support from experienced sleep staff. Study recording will commence as close to the anticipated sleep onset as possible and manually stop recording at sleep offset.

Attended polysomnography collection includes those in unattended polysomnography as described above, with the addition of electroencephalography (C1 and C2 and O1 and O2), EMG Chin (Chin 1 and Chin 2 and Chin 3), EMG diaphragm, snore (microphone), sound level (dB meter), and digital video (audio and visual). Competent sleep technicians will conduct participant setup.

### Outcome Assessment

An oral glucose tolerance test will be undertaken for the assessment of gestational diabetes at 28 weeks (in addition to earlier testing if clinically requested). Collection of fasting blood will be followed by administration of 75 g oral glucose load, with 1 and 2 hours of blood collection. Interpretation will follow the Australasian Diabetes in Pregnancy Society (ADIPS) 2020 guidelines [38].

Blood pressure (BP) will be recorded at each study visit. Diagnosis of HDP will be defined as per the Society of Obstetric Medicine of Australia and New Zealand (SOMANZ) guidelines [39].

Anthropometric measurements (height, weight, and BMI) will be recorded during the randomization visit, and weight will be checked at subsequent study visits by study staff using hospital clinic scales.

### Postpartum Follow-Up

RCT participants will be followed up in the clinic at 6-12 months post partum. At this time point, women will be offered repeat polysomnography, an oral glucose tolerance test (if they developed diabetes and have not already undertaken this in the postpartum period), biomarker blood, and urine collection.

### Statistical Methods

This trial is a feasibility trial, and as such, no power calculations for the RCT were derived. We prespecified to assess the diagnostic accuracy of the home sleep tests as well as the screening questionnaires following the STARD (Standards for Reporting of Diagnostic Accuracy) guidelines. The accuracy will be assessed at various cutoff points using a receiver operating characteristic curve. The area under the receiver operating characteristic curve and positive and negative predictive values in the patient population will be derived. The first recruitment target will be 50 participants, which provides at least 80% power (α=.05) to detect a C-statistic of 0.7 when the allocation ratio is 1 (ie, 50% prevalence) and 0.75 when the allocation ratio is 2 (ie, 20% prevalence). We will be comparing Apnealink Air and SOMTE unattended PSG to attended PSG. Further exploratory analysis will be undertaken to assess whether any factors at booking, including the results of the sleep questionnaire, biomarkers, clinical factors, and history in combination with findings of unattended PSG, Apnealink, or attended PSG, are predictive of poor outcomes (either maternal or fetal, as discussed above). A composite of the combined adverse maternal outcomes and combined adverse fetal outcomes will also be assessed as an outcome. Data will be displayed as mean (SD), 95% CIs, and median (IQR) as appropriate based on data distribution. An intention-to-treat analysis will be undertaken for the primary outcome as well as the secondary outcomes. A per-protocol analysis (for primary and secondary outcomes) will also be undertaken, and both data will be presented. A *P* value of <.05 will be considered statistically significant. Where multiple analyses are undertaken, adjustments will be made for multiple comparisons. Longitudinal analysis of repeated measures will be undertaken where measurements are undertaken several times. Where differences at baseline exist between the groups, adjustments will be made statistically. Where less than 10% of any data point is missing, data will be imputed. We have preplanned an exploratory analysis of flow characteristics of all sleep tests to investigate sub-criterion flow changes related to long-term fetomaternal outcomes.

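### The power statement for the home-sleep-test substudy pairs an allocation ratio of 2 with 20% prevalence, which cannot both hold, and its 80% depends on an undeclared one-sided test in two of the possible scenarios

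*Protocol article*

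**What the plan says.** The Statistical Methods section of the protocol article derives no power for the randomized trial. Its one power statement concerns the accuracy of the home sleep tests (Apnealink Air and SOMTE) against attended polysomnography: "The first recruitment target will be 50 participants", "which provides at least 80% power (α=.05"). Two scenarios follow:

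- "to detect a C-statistic of 0.7 when the allocation ratio is 1 (ie, 50% prevalence");
- "0.75 when the allocation ratio is 2 (ie, 20% prevalence").

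The section does not say whether the 5% level is one- or two-sided, and it gives no null value for the C-statistic. The general rule later in the section, a P "value of <.05 will be considered statistically significant", does not settle the sidedness. The accuracy analysis is described only as follows: "The accuracy will be assessed at various cutoff points using a receiver operating characteristic curve".

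**The concern.** The first scenario fixes the convention: a ratio of 1 is 50% prevalence. On that convention a ratio of 2 is one third, not one fifth. One of the two labels in the second scenario is therefore wrong, and the text does not show which scenario was calculated.

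The claimed power also deserves a check on the usual two-sided reading, because this is the document's only power statement and it supports the first recruitment target. The Informed Consent section says that once home testing is validated, screening will continue with questionnaires and home Apnealink Air only. If prevalence were 20%, the accuracy estimate at 50 women would rest on 10 women with OSA. If it were 33%, it would rest on about 17.

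**Working it through.** **Inputs from Statistical Methods.** n = 50; α = .05; C = 0.70 at ratio 1; C = 0.75 at ratio 2, labelled 20% prevalence. **Assumption:** the null C-statistic is 0.5.

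**Step 1: ratio and prevalence.** With k women without OSA for each woman with OSA, prevalence = 1/(1+k).

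- k = 1: 1/2 = 50% (25/25)
- k = 2: 1/3 = 33% (about 17/33)
- k = 4: 1/5 = 20% (10/40)

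Reading the ratio the other way round gives 2/3 = 67%, so no reading of 2 gives 20%.

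**Step 2: formula.** With n1 women with OSA and n0 without, power = Φ[(C − 0.5 − z·SE0)/SE1], where z = 1.645 (one-sided) or 1.960 (two-sided). The variances are Hanley-McNeil:

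- SE0² = (n1 + n0 + 1)/(12·n1·n0)
- SE1² = [C(1−C) + (n1−1)(a − C²) + (n0−1)(b − C²)]/(n1·n0), with a = C/(2−C) and b = 2C²/(1+C)

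**Step 3: reproduce the plan's figure.**

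*C = 0.70, 25/25.* SE0 = √(51/7500) = 0.0825. SE1² = (0.2100 + 24×0.0485 + 24×0.0865)/625 = 0.00552, so SE1 = 0.0743.
- One-sided: (0.20 − 1.645×0.0825)/0.0743 = 0.866, power 80.7%
- Two-sided: (0.20 − 1.960×0.0825)/0.0743 = 0.517, power 69.7%

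*C = 0.75, 10/40 (20% prevalence).* SE0 = √(51/4800) = 0.1031. SE1² = (0.1875 + 9×0.0375 + 39×0.0804)/400 = 0.00915, so SE1 = 0.0956.
- One-sided: (0.25 − 1.645×0.1031)/0.0956 = 0.841, power 80.0%
- Two-sided: (0.25 − 1.960×0.1031)/0.0956 = 0.502, power 69.2%

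*C = 0.75, 17/33 (a true ratio of 2).* SE0 = √(51/6732) = 0.0870. SE1² = (0.1875 + 16×0.0375 + 32×0.0804)/561 = 0.00599, so SE1 = 0.0774.
- One-sided: (0.25 − 1.645×0.0870)/0.0774 = 1.381, power 91.6%
- Two-sided: (0.25 − 1.960×0.0870)/0.0774 = 1.026, power 84.8%

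(Standard errors are shown rounded; the results use unrounded values.)

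**Step 4: does the method matter?** Two-sided power by other routes:

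| Method | 0.70, 25/25 | 0.75, 10/40 | 0.75, 17/33 |
|---|---|---|---|
| Hanley-McNeil, null and alternative variance | 69.7% | 69.2% | 84.8% |
| Obuchowski binormal variance | 71.8% | 71.6% | 85.8% |
| Mann-Whitney, 10,000 simulated binormal trials | 70.2% | 71.6% | 86.3% |
| DeLong test, same simulation | 73.5% | 75.8% | 88.1% |
| Hanley-McNeil, alternative variance only | 76.8% | 74.3% | 89.8% |

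A normal-theory comparison of two means with the same separation gives 74.6%, 77.0% and 89.2%. In the first two scenarios every method falls short of 80% two-sided. In the third, every method exceeds it.

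**Step 5: what 50 women can detect.** Solving the Step 2 formula for 80% two-sided power gives C of about 0.72 at 25/25, 0.74 at 17/33 and 0.78 at 10/40. Keeping the printed C-statistics with a two-sided test would take 62–64 women for 0.70 at ratio 1 and 65 for 0.75 at 20% prevalence. For 0.75 at ratio 2, 45–48 suffice.

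**The case against.** The text says α=.05 and nowhere says two-sided. With a one-sided 5% test, 50 women give 80.7% and 80.0% in the two scenarios, the second read at 20% prevalence, so the printed claim can be reproduced. The article also condenses a longer protocol that is not shown, and sidedness, null value and variance method are details that such an article may leave out. The calculation serves an accuracy substudy, not the randomized comparison; the move to home Apnealink is tied to no significance test or power level; and the overview under Ethics Approval and Consent to Participate says that the final patient was recruited in December 2022, so a corrected sentence changes no conduct.

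Most of this stands. It rules out a stronger conclusion that a reader might draw, namely that the power is simply 70% instead of 80%. The document does not commit to a two-sided test, and at a true ratio of 2 the claim for 0.75 holds with either sidedness. For the same reason it would be too strong to say that the second scenario reproduces only as a one-sided test at a ratio of 4: the printed ratio of 2 also satisfies it, if the 20% label is the slip.

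The objection does not remove the contradiction between ratio and prevalence, which is a wrong statement in the text shown, not an omitted detail. Nor does it help the C = 0.70 scenario, where the ratio is not in dispute and a two-sided test misses 80% by every method tried. The section reports 95% CIs and an unqualified .05 threshold, so most readers will assume two-sided testing.

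**Conclusion.** The point holds in this form. The second scenario is internally inconsistent: a ratio of 2 means 33% prevalence, and 20% means a ratio of 4. With 50 women and C = 0.75, the choice moves two-sided power from about 85% to about 69%.

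Separately, the 80% claim depends on sidedness for C = 0.70 at 50% prevalence and for C = 0.75 at 20% prevalence. It is about 81% and 80% one-sided, and about 70% and 69% two-sided, with other methods reaching at most about 77%. There is no shortfall for C = 0.75 at a true ratio of 2.

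These figures assume a null C-statistic of 0.5, and the simulations also assume binormal test results. The document does not establish which label is the misprint or which sidedness was used, so the finding is an inconsistency and an ambiguity that decides the claim, not proof that the calculation was wrong. Severity is minor to moderate; the randomized comparison is unaffected.

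**What to change.** Correct the ratio and prevalence pair, name the null value and the sidedness, and restate the figure. Either of these would do:

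- **Two-sided:** With 50 women and a two-sided 5% test against a C-statistic of 0.5, there is 80% power for a C-statistic of about 0.72 at 50% prevalence (ratio 1), 0.74 at 33% (ratio 2) and 0.78 at 20% (ratio 4).
- **One-sided, if that was planned:** Declare it, pair 20% prevalence with a ratio of 4, keep 0.70 and 0.75, and use the same one-sided test in the analysis.

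The cost is a reworded sentence. No further women are needed. Under the two-sided version, the detectable C-statistics at 50% and 20% prevalence become slightly less favourable than printed.

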### Trial Design

Pregnancy-associated obstructive sleep apnea (POSA) is a 2-center randomized controlled feasibility trial. The participants will be recruited following participation in an observational study by our group that assesses diagnostic validation of Apnealink air and Somte devices and long-term fetomaternal outcomes. The participants will also be approached at antenatal visits or called by telephone to assess eligibility. Recruitment at both study sites will be concurrent, and the participants who meet the eligibility criteria based on AHI or RDI results in the observational study will be approached for participation in the RCT.

The RCT will use a parallel group, individually randomized, open-label design with two interventions and one control group (1:1:1), with minimization allocation among the 3 arms stratified for BMI, previous history of preeclampsia, or gestational diabetes mellitus. A total of 48 participants (16 in each arm) will be recruited. Study visits will occur monthly after randomization until 32-week gestation period and fortnightly thereafter until delivery, as is local routine clinical practice for antenatal visits. Data collection will include demographic, clinical and physical details, sleep questionnaire responses, sleep study data, maternal pathology, fetal scans, birth details, maternal and fetal clinical outcomes, sleep therapy compliance, and therapy acceptance questionnaires.

We used the SPIRIT (Standard Protocol Items: Recommendations for Interventional Trials) checklist when writing our protocol [30], which can be found in Multimedia Appendix 3.

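### Covariates are to be chosen by observed baseline imbalance, a rule driven by chance that would in practice not pick up the three minimisation factors

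*Protocol article*

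**What the plan says.** In the protocol article, Statistical Methods makes adjustment conditional on what is seen after allocation: "Where differences at baseline exist between the groups, adjustments will be made statistically". It lists no covariates, does not say what counts as a difference, and does not say how the adjustment is made. No other rule for between-arm covariates appears in the article.

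The allocation sections are specific. Randomization, Allocation, Concealment, and Blinding states: "Randomization will be based on a minimization method with stratification for previous preeclampsia, personal history of gestational diabetes, and BMI≥35". It also sets the tolerance: "A maximum imbalance value of 1 between any of the 3 arms will be used in determining whether a forced allocation". Trial Design names the same factors and gives the size: "A total of 48 participants (16 in each arm) will be recruited". Neither section says whether the factors enter the analysis.

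Between-arm inference is planned: "An intention-to-treat analysis will be undertaken for the primary outcome as well as the secondary outcomes", with a per-protocol analysis alongside, and "A *P* value of <.05 will be considered statistically significant". Development of GDM by 28 weeks is part of the primary outcome.

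**The concern.** Apart from faults in allocation, baseline differences between randomised arms arise by chance. How large such a difference is says nothing about whether the variable predicts the outcome. A rule triggered by imbalance therefore selects on the wrong property, and the model stays unknown until the data are seen. Treatment is open-label and no criterion is written down, so the estimate could depend on that choice.

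The rule also works against the design. Minimisation keeps the three factors chosen for allocation similar across arms, which is what stops them from triggering adjustment. If prognostic factors are balanced by design but left out of the model, their variance stays in the residual although they no longer contribute to the variability of the treatment contrast. The reported standard error is then too large.

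At stake are precision and reproducibility. The Introduction says the efficacy data may be used to design and power a larger trial, so these estimates and their standard errors will be used.

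**Working it through.** **Inputs from the protocol article.** Three arms of 16 (3 × 16 = 48, as stated); three binary minimisation factors; maximum imbalance 1; significance level 0.05, taken as two-sided.

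**Assumptions, not in the article.** Factor prevalences, the share of outcome variance that the factors explain (R²), the number of other baseline variables, and a baseline difference read as P<.05.

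**1. Would the rule select the minimisation factors?** The scheme was simulated as random allocation when the marginal totals differ by at most 1, and otherwise as forced allocation to the lowest arm. With prevalences of 15, 30 and 40%, no factor reached P<.05 for imbalance in any of 3,000 trials. Prevalences of 40, 20 and 30% also gave none. Each factor stayed within about 2 women between arms.

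**2. What would it select instead?** With k independent variables and no true differences, the chance of at least one flag is 1 − 0.95^k:
- k = 5: 22.6%
- k = 10: 40.1% (39.6% simulated)
- k = 20: 64.2%

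**3. Cost of leaving the factors out, continuous outcome with total SD 1.** The unadjusted model reports SE = √(2/16) = 0.354. With the factors fully balanced, the true SD of the contrast is √((2/16)(1 − R²)). The critical value on 45 df is 2.014, so the actual size is about P(|t₄₅| > 2.014/√(1 − R²)).

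| R² | True SD, formula | True SD, simulated | Size, formula | Size, simulated |
|---|---|---|---|---|
| 10% | 0.335 | 0.338–0.339 | 3.9% | 3.8–4.1% |
| 20% | 0.316 | 0.320–0.321 | 2.9% | 2.9–3.6% |
| 30% | 0.296 | 0.298–0.299 | 2.0% | 1.9–2.5% |

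Ranges are across runs of 2,000 to 3,000 trials per setting. Adjusting for the three factors brought the size back to about 5%. Simulated power for a 0.8 SD difference at R² of 10, 20 and 30% was:
- unadjusted: 59–61%, 61–62% and 61–62%
- adjusted: 63–65%, 70% and 74–76%

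**4. The stated rule applied mechanically.** This run used ten other variables unrelated to outcome, and each factor shifted the outcome by one residual SD. At prevalences of 15, 30 and 40% the factor variance is 0.1275 + 0.21 + 0.24 = 0.5775, so R² = 0.5775/1.5775 = 37%, above the range in step 3.

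| Analysis | Type I error | Mean model SE | Empirical SE |
|---|---|---|---|
| Unadjusted | 1.9% | 0.445 | 0.369 |
| Rule: adjust if baseline P<.05 | 1.9% | 0.456 | 0.380 |
| Three factors pre-specified | 5.2% | 0.353 | 0.355 |

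The rule overstates the SE by 0.456/0.380 = 1.20, about 20%. It does no better than no adjustment, and the chance covariates widen the true spread by about 3% (0.380/0.369).

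**5. Binary GDM.** With a linear probability model, an assumed 20-point risk reduction in one arm, and factors explaining about 6, 12 and 21% of variance:
- power was 21, 18 and 14% unadjusted, against 22, 22 and 19% adjusted, a gain of 1 to 5 points
- unadjusted type I error was 5.3, 3.7 and 2.8%

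**The case against.** A reader might infer that the analysis excludes the minimisation factors. The article does not say so. Its sentence can be read as an addition to a base model that is not described, and a statistical analysis plan that is not shown may include the factors. Silence on them is therefore no fault in itself. What stands is that the one rule that is stated would not bring them in, and that its trigger is poor whatever the base model contains.

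A reader might also infer that the rule inflates false positives. The calculations show the opposite: applied mechanically, it is conservative. Distortion from a discretionary choice of covariates is possible but was not quantified.

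The power figures do not carry over to GDM, where the comparison has little power with or without adjustment. The figure of 64% needs 20 independent variables tested at P<.05. The article sets no such test, and clinical baseline variables are correlated.

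Finally, this is a feasibility study: "This trial is a feasibility trial, and as such, no power calculations for the RCT were derived". No decision rule in the article turns on an adjusted P value. That limits the consequence, but it does not make the rule sound, because tests at .05 are planned and the estimates are meant to inform a larger trial.

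**Conclusion.** The point holds against the stated rule: the choice of covariates is left to chance imbalance, with no named variables and no criterion. That the rule would in practice not select the minimisation factors is well supported, since none was flagged in any simulated trial. That the factors will be missing from the analysis is conditional on no other document adding them.

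If they are missing, the harm is lost precision and conservative tests. For continuous secondary outcomes it ranges from slight at 10% explained variance (size about 4%) to material at 30% (size about 2%, and roughly 13 points of power for a 0.8 SD difference, 61% against 74% in one run). For GDM it is small. These sizes rest on the assumed prevalences and explained variance. The dependence of the model on the data does not. In a feasibility trial this should be put right, but it does not threaten the study.

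**What to change.** Replace the sentence in Statistical Methods with a fixed rule, for example:

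> Between-arm comparisons adjust for the three minimisation factors and, for continuous outcomes measured at the randomisation visit, the baseline value, whatever the observed balance. Baseline differences are described, not tested, and do not change the main model.

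For GDM, keep the adjustment small (for example previous GDM and BMI≥35), use a pre-specified method suited to few events, and show the unadjusted result beside it. The choice of estimator is open; what matters is that it is fixed in advance. Any adjustment for an observed imbalance should be a labelled sensitivity analysis.

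The cost is wording only. The factors are recorded for allocation, and weight and uterine artery pulsatility index are measured at the randomisation visit. Recruitment ended in December 2022, so the rule should be dated and fixed before between-arm results are examined. If an analysis plan already names these covariates, the article's sentence should be brought into line with it.
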